#### 2.6.1. Absolute Contraindications for Exercise [35,36,37]

Progressive worsening of exercise tolerance or dyspnea at rest over previous 3–5 daysPresence of critical narrowing of the left coronary artery (obstructive left main coronary disease)Unstable anginaUncontrolled cardiac arrhythmiaAcute endocarditis, myocarditis or pericarditisModerate to severe aortic stenosisDecompensated heart failureAcute pulmonary embolism or deep-vein thromboembolismAortic dissectionHigh-grade atrioventricular blockHypertrophic obstructive cardiomyopathyRecent cerebrovascular accident (CVA) or transient ischemic attackUncontrolled diabetesRetinopathySevere autonomic or peripheral neuropathyAcute systemic illness or feverAcute or chronic renal failurePulmonary fibrosis or interstitial lung diseaseRecent myocardial infarction (<4 weeks), coronary artery bypass grafting (<4 weeks) or percutaneous coronary intervention

#### 2.6.2. Indications for Temporary Cessation

Symptoms such as angina, shortness of breath, dizziness (lightheadedness), confusion or signs of poor blood circulationOxygen saturation < 88%Increase in blood pressure > 220/105 mmHgDrop in systolic blood pressure > 10 mmHgHR decrease with higher load or development of any atypical arrhythmia

The therapist will be alert for any new symptoms or adverse events during exercise to discontinue the program and recommend referral to the physician and further investigation. Every adverse event will be recorded on the Athlete Monitoring app.

### 2.7. Outcome Measures

For all scales and questionnaires, permission to use has been granted after personal communication with the creators or with the team that has carried out the validation in the Greek population. All outcome measure measurements will be performed by an examiner blinded to the allocation group of the assessed (single-blinded). The demographic characteristics, fracture type, surgical technique and pre-fracture level of independence will be collected. All measurements will be performed in a lab setting.

The pre-fracture level of independence will be evaluated using the New Mobility Score (NMS). The NMS consists of three questions assessing the ability to walk in daily activities. The NMS is completed by the patient or by the caregiver in cases of cognitive impairment. The patient is asked to answer for pre-fracture walking ability the following: (1) able to move around the house (indoor walking), (2) able to go outside the house (outdoor walking) and (3) able to go shopping (walking while shopping). Each question can be scored from 0 to 3 points based on the patient’s self-reported ability, where 0 points correspond to an inability to perform, 1 point to assistance from another person, 2 points to use of an aid and 3 points to independent performance without assistance. The total score ranges from 0 to 9 points, with a score of 6 points or less indicating low functional capacity, while more than 6 points reflects a high level of pre-fracture function in patients with hip fractures. A score equal to or greater than 7 points justifies the rapid release of the patient from the hospital without the need for further in-hospital rehabilitation after surgery [38,39].

Table 1 represents the scheduled timeline of all the outcome measures.

#### 2.7.1. Basic Mobility

Basic mobility will be evaluated with the Cumulated Ambulation Score (CAS) and Timed-Up and Go (TUG). In orthopedic wards, the CAS is a reliable and valid measure for measuring patients’ mobility and is strongly recommended as an evaluation test by the Clinical Practice Guidelines of the American Physical Therapy Association (APTA) [1]. The CAS is an ordinal 3-point scale assessing a patient’s ability to get in and out of bed, sit to stand from a chair and walk inside a room. The scale for each test is scored from 0 to 2, with 0 meaning “unable to perform”, 1 “performing with assistance” and 2 “performing unassisted-independently”. The total 3-day CAS has a stronger predictive value than the 1-day CAS [40]; it is based on the sum score of the first three postoperative days, with a minimum value of 0 and a maximum value of 9; a higher score indicates a better prognosis for the total 3-day CAS [41,42]. An assessment will be performed on postoperative days 1, 2 and 3, as recommended by the literature, and at four weeks postoperatively.

Mobility will also be assessed with the TUG test. This test was designed to assess mobility in the elderly. The TUG test is a sensitive measure for predicting fall risks after hip fracture surgery [43]. It is a simple, easy-to-use functional performance test. The time required for the subject to rise from the chair, walk a distance of three meters, turn, walk back to the chair and sit is recorded. A chair (with back and supports), a tape measure, a tape and a clock or stopwatch are required. The assessment will be performed at 4, 8, 26 and 52 weeks postoperatively.

#### 2.7.2. Aerobic Capacity

The distance covered with the 6-minute walking test (6MWT) will be evaluated to assess their aerobic capacity. The 6MWT is an easy-to-use and reliable functional capacity assessment test. It is widely used and considered ideal for patients with respiratory, cardiovascular and other diseases characterized by reduced physical fitness [44,45]. It is simple to perform, easily understood by patients and reflects patients’ ability to cope with their daily activities, which mostly require submaximal work. The distance covered during the 6-minute walking test has been found to be positively correlated with the VO_2_ peak [46].

Patients are asked to walk as far as possible for 6 min. The patient will be allowed to use an external aid. There is strong evidence for the reliability and validity of the test in patients after hip fractures. Overgaard et al. [47] reported minimum detectable changes (MDC) without aid at 59.4 m and with aid at 49.8 m. The test will be performed along a 25 m aisle, and the HR will be simultaneously recorded using a HR monitor chest strap (Polar H10, Polar Electro, Kempele, Finland). The assessment will be performed at 4, 8, 26 and 52 weeks postoperatively.

#### 2.7.3. Lower Extremity Function

The modified Harris Hip Score (mHHS-Gr) and Lower Extremity Functional Scale (LEFS-Gr) will be used to determine lower extremity function. The mHHS [48] and LEFS [49,50] are valid and accurate self-reported measures of hip pain, function and lower extremity function. The mHHS has been used in femoral neck fractures with high discriminative capability between groups with and without complications at four months follow-up (95% CI Area Under the Curve: 0.63–0.89) and with good responsiveness from 4 to 12 months follow-up [51]. On the mHHS, one question assesses pain (score from 0–44) and seven questions functioning (score from 0–47). The total score will be multiplied by 1.1, resulting in a range from 0 to 100, with a score of 100 representing the worst possible hip pain and function. The LEFS comprises 20 multiple-choice questions scored on a 5-point scale (0–4: 0 = very high degree of difficulty to 4 = no difficulty, with a maximum score of 80). Assessment of the mHHS and LEFS will be performed on day 1 of admission to assess the pre-fracture level of independence (retrospective narrative) and at 4, 8, 26 and 52 weeks postoperatively.

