#### 2.8.2. Data Analysis

Descriptive statistics will be used to summarize the baseline characteristics of the patients participating in each group. Continuous variables will be presented with the mean and standard deviation or median and interquartile ranges (IQR) if they do not follow a normal distribution. Categorical variables will be presented with absolute and relative frequencies (n, %). The Kolmogorov–Smirnov test will be performed to check for normality. Based on the normal or non-normal distribution of the sample, a *t*-test or Mann–Whitney test will be performed to compare the means or medians of the two groups, respectively. The chi-square test will be used to identify differences in the categorical variables between the two groups. A subgroup analysis will be performed a posteriori for the different surgical techniques used for all variables.

To detect confounding factors that may affect the functional tests (CAS, 6WMT and TUG), multiple linear regression will be performed after first performing the relevant check on whether the conditions are met to consider the linear regression results reliable. If the necessary conditions are not met, the necessary transformations of the dependent variables will be carried out.

To test the change of the parameters to be measured at multiple time points (e.g., albumin, functional score, etc.) and to compare the change between the intervention group and the control group, we will perform an analysis of variance for repeated measurements (repeated measures ANOVA).

Additionally, the time to occurrence of an event (e.g., death, readmission to hospital, thrombosis, etc.) will be presented with a Kaplan–Meier survival curve. To highlight the factors related to the time of occurrence of an event, semiparametric (Cox proportional hazard models) or parametric survival analysis models (e.g., Weibull, exponential, etc.) will be performed, as will result from the analysis that will be done.

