## 3. Discussion

This study has two primary purposes. First, to study the effect of a preoperative aerobic exercise program with a portable upper extremity cycle ergometer on immediate postoperative mobility. Second, to investigate the additional effect of an 8-week postoperative aerobic exercise program with a portable upper extremity cycle ergometer on the walking distance at 8 weeks after surgery. This study also has a number of secondary objectives. Regarding the preoperative exercise program evaluation of the effect of the preoperative program on surgical stress (via blood lactate levels), perioperative bleeding and transfusion requirements, hemostasis factors will be evaluated, in addition to, an evaluation of the effect of the postoperative program in the short and long term: lower extremity functionality, aerobic capacity, nutritional status, hemostasis factors, mortality, rehospitalization and complications related to surgery and hospitalization (thrombotic and thromboembolic events).

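### The stated direction of the modified Harris Hip Score (100 = worst) is very probably inverted and should be checked and corrected before analysis

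*Protocol article*

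**What the plan says.** Section 2.7.3 names two self-reported instruments for lower extremity function, the mHHS and the LEFS.

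For the mHHS, "one question assesses pain (score from 0–44) and seven questions functioning (score from 0–47" points. The sum is then scaled up by a factor of 1.1, a step that the article describes as "resulting in a range from 0 to 100, with a score of 100 representing the worst possible hip pain and function". No other section gives a direction for this score, so this sentence is the article's only rule for reading it.

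For the LEFS, each of 20 items runs from "0 = very high degree of difficulty to 4 = no difficulty, with a maximum score of 80".

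Both scales are taken at admission as a recalled pre-fracture status and again at weeks 4, 8, 26 and 52 (Section 2.7.3 and Table 1). The Discussion places lower extremity functionality among the secondary objectives, as part of "an evaluation of the effect of the postoperative program in the short and long term: lower extremity functionality, aerobic capacity" and other outcomes. For parameters measured at several time points, Section 2.8.2 says that, "to compare the change between the intervention group and the control group, we will perform an analysis of variance for repeated measurements". It does not say which direction of change counts as benefit.

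**The concern.** The wording that sets the direction of the mHHS fits poorly with the scoring described just before it. Points are given on a functioning component, they are summed without reversal, and the highest total is then called the worst state. The scale paired with it for the same construct runs the other way, and the article does not remark on this.

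At stake is how a secondary outcome is read. The planned test can show that the arms differ on the mHHS, but only the stated direction tells the reader which arm did better. If that direction is inverted and someone relies on it, a better result in the exercise arm could be described as a worse one, and the mHHS and LEFS could seem to disagree when they do not. If the data were instead recoded to match an inverted sentence, the scores would no longer be comparable with mHHS scores produced by the instrument's own rules.

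**Working it through.** **Inputs.** From Section 2.7.3: mHHS pain 0 to 44, mHHS functioning 0 to 47, multiplier 1.1, no reversal step, stated range 0 to 100 with 100 as worst; LEFS with 20 items scored 0 to 4. From Sections 2.7 and 2.7.1: the directions of the New Mobility Score (NMS), the Cumulated Ambulation Score (CAS) and the Timed-Up and Go (TUG).

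**Step 1: the stated range.** Minimum: (0 + 0) × 1.1 = 0. Maximum: (44 + 47) × 1.1 = 91 × 1.1 = 100.1, which is 100 to the nearest whole number. The range is reproduced, and the rounding is no fault. The result is the same whichever end is best, so arithmetic alone cannot settle the direction.

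**Step 2: what the label requires.** The two components are added, so they must run the same way. If one counted severity and the other counted ability, a total of 100 would be neither the best nor the worst state. For 100 to be worst, 44 must mean the most pain and 47 must mean the poorest function. The pain component could be read either way from its description. The functioning component would have to count disability, which the text does not say. With no reversal stated, the more natural reading is that more functioning points mean better function. The pain points must then reward absence of pain, and 100 is the best state.

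**Step 3: the other rated scales in the article.**

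| Scale | Section | Direction as described |
|---|---|---|
| LEFS | 2.7.3 | 20 × 4 = 80 means no difficulty on any item: higher is better |
| NMS | 2.7 | above 6 of 9 means high pre-fracture function: higher is better |
| CAS | 2.7.1 | higher means better prognosis: higher is better |
| mHHS | 2.7.3 | 100 is worst: higher is worse |

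The mHHS is the only rated mobility or function scale described as running downward. This supports an inversion but does not prove it.

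**Step 4: the consequence if the label is inverted.** Let a and b be the mean scores in the control and exercise arms. Reading the scale from the wrong end amounts to replacing each score x by 100 − x. The difference becomes (100 − b) − (100 − a) = −(b − a). The size is unchanged and the sign flips. Two-sided results of the t-test and the Mann–Whitney test, and the F tests of the repeated measures ANOVA, do not change under this replacement. The sample size in Section 2.8.1 rests on the 3-day CAS and the six-minute walk only, so it does not change either.

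**The case against.** The strongest reply is that the article never says which answers earn 44 or 47 points. A reader might infer that the documents prove the direction wrong, but that step needs the instrument's own scoring rules, which lie in a cited source that is not at hand. This objection stands. It limits the claim to a very probable inversion.

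It is also fair to say that two measures of one domain may run in opposite directions. Section 2.7.1 already pairs the CAS, where higher is better, with the TUG, a time, where lower is better. The contrast with the LEFS is therefore a hint and not a contradiction.

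A reader might further infer that a benefit would be reported as harm. The documents do not support that. It would take conventional item scoring and, in addition, an analyst who reads results from this one sentence. Section 2.7 says that permission for the scales came from their creators or from the Greek validation teams, so the investigators have a direct route to the scoring rules.

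What the reply does not remove is the sentence itself. The article positively states a direction, so this is not detail left to a fuller document, and the stated direction fits poorly with the scoring it describes.

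**Conclusion.** The point holds in a limited form. The label that makes 100 the worst mHHS state is very probably inverted, judged from the unreversed sum with its functioning points and, more weakly, from the direction of the other rated scales. Certainty would need the item anchors.

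If it is inverted and used for interpretation, the direction of the between-group mHHS difference could be misread at four postoperative visits, on one of the two instruments named for lower extremity function. The effect is on sign only. The magnitude of differences, two-sided p-values, the two primary outcomes (3-day CAS and six-minute walk distance) and the sample size of 116 are untouched. For a secondary outcome with a simple remedy, the severity is minor to moderate.

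**What to change.** 1. Check the mHHS direction against the validation cited in Section 2.7.3 and the scoring rules of the Greek version in use.
2. If the inversion is confirmed, correct the sentence so that 0 is the worst and 100 the best state. If it is not, add the item anchors that make 100 the worst.
3. State the direction of benefit for both the mHHS and the LEFS in the same paragraph.
4. Verify before analysis that the database and scoring code use that direction.

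The cost is one corrected sentence, a short statement of direction and a check of the scoring code. No new data are needed, and neither the design nor the sample size changes.

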#### 2.7.4. Blood Lactate Concentration

A hand-held lactate measuring analyzer (Lactate Scout+, EKF Diagnostics, Leipzig, Germany) with device-compatible test strips (sensors) will be used to obtain and analyze the lactate concentration of the capillary blood. Blood will be collected from the nail phalanx of the index hand with a puncture pen using sterile disposable lancets. Before each puncture, the nail phalanx will be antiseptic with gauze soaked in an alcoholic solution ≥70%. The measured range is from 0.5 to 25.0 mmol/L. The measurement accuracy is approximately ±3% when the hematocrit (Hct) ranges from 35 to 50% and ±4% when Hct > 50% [52,53]. The capillary blood lactate will be taken before and after each exercise session (only intervention group) to indicate the exercise intensity. The assessment will be performed on the day of admission, intraoperatively (at the beginning, 30 min later and at the end of the surgery) and 12 h postoperatively.

#### 2.7.5. Nutritional Status

To assess the patient’s nutritional status, the levels of albumin and prealbumin in the blood will be assessed. A blood sample will be collected and analyzed in the laboratory on the day of admission; one day before surgery; on the third postoperative day and at 1, 4, 8, 26 and 52 weeks postoperatively.

#### 2.7.6. Blood Sample Collection and Hemostatic Profile

The following factors will be evaluated: platelet functionality with a PFA-200 analyzer, hemostatic profile using viscoelastic techniques (ROTEM), tissue plasminogen activator (tPA), plasminogen activator inhibitor- 1 (PAI-1), the thrombin–antithrombin complex (TAT), the endogenous thrombin potential (ETP), fibrinogen, D-dimers, thrombomodulin and von Willebrand factors (vWF:Antigen and vWF:Activity plasma levels) as markers of endothelial function.

The standard range for fibrinogen is between 200 and 400 mg/dL (2.0 and 4.0 g/L). Plasma fibrinogen concentrations will be determined by modifying the Clauss technique with the Fibrinogen Multifibren U reagent (Siemens Healthcare Diagnostics, Marburg, Germany). Increased fibrinogen levels correlate substantially with inflammatory indicators, illness severity and thrombotic propensity.

The reference concentration of a D-dimer is <250 ng/mL. The particle-enhanced immunoturbidimetric INNOVANCE D-dimer assay (Siemens Healthcare Diagnostics, Marburg, Germany) will be used to evaluate the D-dimers. In addition to the value of normal D-dimer measurements in allowing the exclusion of venous thromboembolism (VTE) or pulmonary embolism (PE), the D-dimer test helps clinicians stratify patients with the risk for deep venous thrombosis (DVT), because high levels of D-dimer in the blood are associated with a major clot. Hence, elevated D-dimer levels indicate a hemostatic imbalance.

Normal thrombomodulin (TM) levels fluctuate between 3.1 ± 1.3 ng/mL and range from 3 to 300 ng/mL. For the measurements, a TM sandwich ELISA double antibody kit will be used. By controlling the coagulation system, TM, which is mainly expressed on the endothelium, plays a vital role in maintaining the vascular homeostasis. During the hypercoagulable condition after endothelial damage, TM is released into the intravascular space, suggesting endothelial dysfunction-related disruptions of the hemostatic balance. In addition, TM decreases blood coagulation by converting thrombin from a procoagulant to an anticoagulant enzyme, and it has the capacity to control intravascular damage via its pleiotropic actions.

vWF:Antigen (Ag) and vWF:Activity (Ac) are used as measures of platelet and endothelial dysfunction impacting the hemostatic equilibrium. The plasma levels of vWF:Ag and vWF:Ac will be measured using an automated latex enhanced immunoassay (HaemosIL^TM^ assay, Instrumentation Laboratory Corporation, Lexington, KY, USA) using IL (Instrumentation Laboratory) coagulation equipment (ACL TOP). The vWF:Ac will be evaluated by measuring the differences in turbidity caused by the latex reagent’s agglutination. A monoclonal anti-VWF antibody immobilized on the latex reagent interacts with the vWF in the blood sample. The agglutination is proportional to the vWF:Ac and is determined by the decreased light transmission resulting from the aggregates. The results will be presented as a percentage of the normality.

For the ROTEM analysis, within 90 min after blood collection, a citrated tube will be immediately filled with blood and will be analyzed in a ROTEM analyzer. Blood held at room temperature for up to 120 min after collection does not impact the ROTEM findings. Blood samples will be examined using a ROTEM analyzer (ROTEM delta, Tem Innovations GmbH). The ROTEM analysis includes preoperative EXTEM and INTEM testing and postoperative INTEM assays. The following EXTEM and INTEM parameters will recorded: clotting time (CT, seconds), the time from the beginning of measurement until the formation of a clot 2 mm in amplitude; clot formation time (CFT, seconds), the time from CT (amplitude of 2 mm) until a clot firmness of 20 mm was achieved; amplitude recorded at 10 min (A10, mm); an angle (a°), the angle between the central line and the tangent of the TEM tracing at the amplitude point of 2 mm describing the kinetics of clot formation; maximum clot firmness (MCF, mm), the final strength of the clot; and the lysis index at 60 min (LI60, %), which is the percentage of remaining clot stability in relation to the MCF following the 60-min observation period after CT, which indicates the speed of fibrinolysis [10].

Blood samples will be collected on the day of admission; one day before surgery; on the third postoperative day and at 1, 4, 8, 26 and 52 weeks postoperatively.

#### 2.7.7. Mortality and Incidence of Thrombotic/Thromboembolic Events

All thrombotic (e.g., myocardial infarction and stroke) and thromboembolic events (e.g., pulmonary embolism and deep vein thrombosis) will be recorded throughout the study. All-cause mortality will also be documented. Follow-up will take place up to 1 year after surgery.

